**Methods:**

This German study consists of a low-threshold online screening for PACS where positively screened participants will be supported throughout by personal pilots. The personal pilots are aimed at empowering patients and helping them to navigate through the study and different treatment options. Patients will then be randomly assigned either to an intervention group (IG) or an active control group (ACG). The IG will receive a comprehensive assessment of physiological and psychological functioning to inform future treatment. The ACG does not receive the assessment but both groups will receive a treatment consisting of an individual digital treatment program (digital intervention platform and an intervention via a chatbot). This digital intervention is based on the needs identified during the assessment for participants in the IG. Compared to that, the ACG will receive a more common digital treatment program aiming to reduce PACS symptoms. Importantly, a third comparison group (CompG) will be recruited that does not receive any treatment. A propensity score matching will take place, ensuring comparability between the participants. Primary endpoints of the study are symptom reduction and return to work. Secondary outcomes comprise, for example, social participation and activities in daily life. Furthermore, the feasibility and applicability of the online screening tool, the holistic assessment, digital trainings, and personal pilots will be evaluated.

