### Consequences for social participation and quality of life

In Bavaria/Germany, where the study is being carried out, about 20,000 patients with PACS are expected according to the data of the Association of Statutory Health Insurance Physicians of Bavaria [21]. Thus, a considerable need for care must be anticipated. In addition to the individual consequences for the affected patients, such as reduced quality of life and poor health, the loss of earnings can have considerable consequences for the individual, their social network, and society in addition to the social security system in Germany (cf. [20]). A survey with 3762 patients found that 7 months after acute COVID-19, only 27.3% were working the same number of hours as before infection, 22.3% were not working at all and 45.6% had reduced their number of hours [18]. Hence, it is crucial that workability and return to work (RTW) are considered in the treatment of PACS. Preventing the loss of employability and restoring workability is a crucial aim in medical rehabilitation which might be an effective treatment option and hence needs to be adapted to the requirements of patients suffering from PACS [22].

Employment and workability are important parts of social participation [23]. Work life poses an imperative indicator of social life which is endangered if societal requirements cannot be fulfilled. Additionally, a reduced cognitive or physical capacity and performance, for example, due to PACS such as fatigue and brain fog can further decrease patients’ social participation, potentially leading to isolation and further deterioration of health and wellbeing. In turn, reduced participation is related to a decrease in mental health and quality of life. Ismael and colleagues have found that approximately 26% of COVID-19 patients suffer from psychological symptoms including stress and PTSD [24] as well as neuro-psychological symptoms such as the inability to concentrate or language impairments [25]. Mental health problems in PACS patients are common and affect patients’ quality of life [26].

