Internal diagnostics	• Echography • Carotis-duplex sonography

The results of the assessment for each professional group will be handed to a clinician, who is then able to make a holistic assessment of whether PACS is present or not. These assessments are also summarized to form a holistic treatment plan, which synopsizes the findings and lists the indicated medical and therapeutic measures. These recommendations will be made visible for the personal pilot, and subsequently made available to the attending outpatient doctor.

The prescription of necessary treatments and aids, as well as the recommendation of digital interventions already take place within the framework of discharge management. If the need for a rehabilitation measure is determined, this will be communicated to the patient directly in a way to enable him/her applying for rehabilitation treatment and finding the most appropriate treatment within Germany (also with the help of the personal pilot).

Using such an approach allows us to test Hypothesis 2, that a comprehensive assessment can determine rehabilitation or remedial needs and the leading rehabilitation indication. To assess the applicability of this hypothesis, we will consider a comparison of test–retest reliabilities of the degree of experienced symptoms in the IG compared with the ACG and the CompG. Furthermore, the assessment allows us also to test Hypothesis 5 that an interdisciplinary treatment pathway empowers the patient. To assess the applicability of this hypothesis we will check whether IG, ACG and CompG differ in terms of the development of symptoms, increased activities of daily lives, RTW and increased social participation. To do so, we will consider MANOVA and repeated measurement ANOVA analyses.

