For the *summative effectiveness evaluation*, the primary endpoint is the symptom reduction regarding PACS, and RTW. Secondary outcomes include social participation, health-promoting behaviors, and activities of daily living (ADL) as well as mental health and life satisfaction/quality of life. Survey and documentation of all endpoints are conducted by means of questionnaires and/or interviews with study participants who have completed interventions over the course of the project as described above. In addition, possible moderators (especially socio-demographic data) and mediators (e.g., motivation, self-efficacy, and coping strategies) are quantitatively reviewed and added to the analyses. An overview of the measures is provided in Table 2 and Additional file 1.

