### Statistical analysis

#### Sample size planning

With an alpha error of 0.05 and a power of 68%, a sample of *N* = 132 (*n* = 66 in the IG and *n* = 66 in the ACG) is required to be able to demonstrate an effect of *d* = 0.15. The evaluation will be conducted statistically using a Multivariate Analysis of Variance (repeated-measures MANOVA: within-between interaction; power analysis calculated with G*Power). In addition to classical significance tests (*p*-value of a two-sided test below 0.05), the clinical significance will be calculated with effect sizes.

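### Two primary endpoints share one unadjusted 0.05 threshold with no success rule, and return to work is assigned to (M)ANOVA although entry does not require work absence or reduced hours

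*Protocol article*

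**What the plan says.** The abstract of the protocol article (Methods) says "Primary endpoints of the study are symptom reduction and return to work". The section Evaluation concept repeats this: "the primary endpoint is the symptom reduction regarding PACS, and RTW". Social participation and activities of daily living (ADL) are named there as secondary.

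The section Sample size planning gives one calculation, for a repeated-measures MANOVA (within-between interaction) with 66 patients in the intervention group (IG) and 66 in the active control group (ACG). It opens "With an alpha error of 0.05 and a power of 68"% and says that this sample "is required to be able to demonstrate an effect of *d* = 0.15". The significance criterion is a *p*-"value of a two-sided test below 0.05". The effect is not tied to either primary endpoint. The text does not split alpha, order the endpoints, or say whether one or both must be significant.

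For Hypothesis 5 (section 2, Comprehensive assessment program), symptoms, ADL, return to work (RTW) and social participation form one list compared across IG, ACG and the untreated comparison group, and "we will consider MANOVA and repeated measurement ANOVA analyses". Section 3 (Digital therapy offers) does the same for Hypothesis 3, and Type of statistical analysis used repeats the method.

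Table 1 sets no criterion on being off work or on reduced hours. Its only work-related entry excludes certain occupations. The background cites a survey in which, 7 months after infection, "only 27.3% were working the same number of hours as before infection", 22.3% were not working and 45.6% had reduced their hours.

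**The concern.** Two linked problems follow from the methods that the article names.

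The first is what counts as a positive trial. With two primaries, one threshold and no rule, there are two natural readings, and each has a defect:
- Separate repeated-measures ANOVAs, with either endpoint sufficient, raise the chance of a false claim above 5%.
- One omnibus MANOVA over the whole list keeps 5% under the global null, but secondary outcomes alone could make it significant. If separate ANOVAs then follow at 0.05 each, a real effect on a secondary outcome opens the gate, and the two primaries are again tested without adjustment.

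The second is RTW. A return is possible only for someone who is off work or working less. Nothing in eligibility ensures this, the article's own background suggests that patients with unchanged hours are common, and no stated analysis separates them. If they are included, they contribute no treatment effect. If RTW is recorded as yes/no, (M)ANOVA is also a poor match for its scale. At a planned power of 68% the trial has little room for dilution.

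**Working it through.** **1. The plan's own figure.** Read as a plain two-group comparison, d = 0.15 with 66 per group gives 13.6% power, so that reading does not reproduce 68%. For the within-between interaction, take λ = N·m·f²/(1−ρ), with m measurements and correlation ρ, in a noncentral F test with two groups:
- f = 0.15, m = 2, ρ = 0: λ = 132·2·0.0225 = 5.94, power 67.7%.
- f = d/2 = 0.075, m = 3, ρ = 0.7: λ = 132·3·0.005625/0.3 = 7.425, power 67.2%.

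Both are close to 68%, but neither set of assumptions is stated. Either way, the figure is for one test at 0.05.

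**2. Error for two separate tests at 0.05 when either suffices.** If independent: 1 − 0.95² = 9.75%. If correlated: 1 − P(|Z₁| < 1.96 and |Z₂| < 1.96), bivariate normal:

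| Correlation | 0 | 0.5 | 0.7 | 0.9 |
|---|---|---|---|---|
| Family-wise error | 9.75% | 9.1% | 8.3% | 7.0% |

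If both must be significant, no adjustment is needed.

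**3. Dilution of RTW, yes/no illustration.** The assumptions are mine, except where a source is named:
- RTW is yes/no, with 50% (IG) vs 30% (ACG) among those at risk.
- A share q is unaffected and counts as working in both groups.
- The split is 44/88, because the dice rule in Evaluation concept sends 1–2 to IG and 3–6 to ACG (132/3 and 2·132/3).

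Rates in everyone are q + (1−q)·0.5 and q + (1−q)·0.3. Power = Φ[(Δ − 1.96·s₀)/s₁], where s₀ is the pooled and s₁ the unpooled standard error.

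At q = 0.273 (the cited survey), 132·0.727 ≈ 96 patients are at risk, split 32/64.
- Restricted: Δ = 0.20, s₀ = 0.1043, s₁ = 0.1053, so Φ(−0.04) = 48%.
- Everyone: 0.6365 vs 0.4911, Δ = 0.1454, s₀ = 0.0920, s₁ = 0.0900, so Φ(−0.39) = 35%.

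| Unaffected share | Difference in everyone | Power, restricted (n) | Power, everyone (44/88) |
|---|---|---|---|
| 5% | 19.0 points | 59% (42/84) | 56% |
| 10% | 18.0 points | 57% (40/79) | 50% |
| 27.3% | 14.5 points | 48% (32/64) | 35% |
| 50% | 10.0 points | 36% (22/44) | 20% |

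The stated 66/66 split changes little: at 27.3%, the same formula gives 52% restricted (48/48) and 39% in everyone.

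**4. Dilution of RTW, continuous score.** Use the first setting in step 1. If 27.3% show no effect, f falls to 0.15·0.727 = 0.109 and power from 68% to about 42%. Restricting to 96 patients at f = 0.15 gives about 54%. With everyone included, power is about 59% at 10% unaffected and about 23% at 50%. The direction does not depend on yes/no coding.

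**The case against.** A reader might infer that each primary endpoint gets its own 0.05 test and that the error rate is therefore nearly 10%. The article does not say this. The sample size rests on one MANOVA, and nothing says that either endpoint alone counts as success. One omnibus test has 5% error under the global null, and a both-must-succeed rule needs no adjustment. The inflation is therefore conditional. Nor does the article state that all listed outcomes enter one MANOVA, so the pooling is likewise one of two readings. Neither reading, however, gives a 5% test that is about the primary endpoints.

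A reader might also infer that RTW will be analysed in everyone, including patients who never stopped working. That too is unstated. Trial eligibility is not the analysis set for one endpoint, and both that set and a multiplicity rule could stand in an analysis plan not shown. The RTW measure is referred to Additional file 1, also not shown. If it is a work-ability score or hours worked, analysing all patients can be defended. What stands is that the article itself assigns RTW to (M)ANOVA alongside outcomes that apply to everyone, while admitting patients for whom return has no meaning.

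The size of the dilution is also open to challenge. The 50% vs 30% rates are illustrative. The 27.3% comes from a survey at 7 months, whereas this trial admits untreated patients aged 18 to 60 from 4 weeks after infection and excludes some occupations. At an unaffected share of 5% the gap nearly closes (59% vs 56%).

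Making RTW secondary would also settle the multiplicity question, but that is a design preference and is not needed.

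**Conclusion.** The point holds in a conditional form. It is established that two primary endpoints share one unadjusted two-sided 0.05 threshold and a single-test sample size, with no success rule, and that both are listed with secondary outcomes for the same methods. The consequence is either a family-wise error of 7.0% to 9.75%, if separate tests are run and either suffices, or an omnibus result that cannot be attributed to a primary endpoint.

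It is also established that RTW is assigned to (M)ANOVA without an entry requirement on work status. The loss of power is a possibility whose size depends on the unaffected share: about 7 points at 10%, 13 to 14 points at 27.3% and 15 to 16 points at 50%. This assumes yes/no RTW, 50% vs 30% among those at risk, and 44/88. The documents do not support the flat statements that error is 9.75% or that every patient is counted for RTW.

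**What to change.** Keep both primary endpoints, and state:

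1. **Success rule.** Test symptom reduction and RTW separately, IG against ACG, with Holm at an overall two-sided 0.05; or state that both must be significant at 0.05.
2. **Content of the primary test.** Leave ADL and social participation out of it and analyse them as secondary.
3. **RTW population and method.** Define RTW. Analyse it in patients off work or on reduced hours at T1, with a model suited to its scale (logistic regression if yes/no). If RTW is a work-ability or hours score, analyse all patients with adjustment for the T1 value.

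These are changes of wording to the analysis, not to conduct. The costs are in power. Holm tests the smaller p-value at 0.025, where power at N = 132 is about 57% rather than 68% under either setting that matches the stated figure; about 166 patients would keep 68% at 0.025. Under both-must-succeed with 68% power for each, joint power is 0.68² = 46% if the endpoints are independent, and higher if they are positively correlated. The RTW analysis set becomes smaller, about 96 of 132 if the survey's 27.3% applies, although in the illustration the restriction gains more power than it loses.

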### Statistical analysis

#### Sample size planning

With an alpha error of 0.05 and a power of 68%, a sample of *N* = 132 (*n* = 66 in the IG and *n* = 66 in the ACG) is required to be able to demonstrate an effect of *d* = 0.15. The evaluation will be conducted statistically using a Multivariate Analysis of Variance (repeated-measures MANOVA: within-between interaction; power analysis calculated with G*Power). In addition to classical significance tests (*p*-value of a two-sided test below 0.05), the clinical significance will be calculated with effect sizes.

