### Evaluation concept

A longitudinal randomized control trial design is used in this project with a three-group pretest–posttest procedure. Whereas the CompG will be recruited with different links via online invitations (e.g., via social media campaigns), the IG and the ACG are recruited with another separate link. After agreeing to take part in the study, participants will be randomized by throwing a dice. Patients for whom a 1 or 2 was rolled are placed in the IG and patients for whom a 3–6 was rolled are placed in the ACG. If a randomization cannot be realized (e.g., because they cannot take part in the stationary assessment due to organizational limitations), patients will be allocated to the ACG but will be marked for statistical analyses. Methodically, a propensity score matching will be used between the IG and the CompG to ensure the comparability of these groups (i.e., participants will statistically be matched by various person-related criteria such as age and sex). All groups are repeatedly interviewed with similar instruments in each group (see Table 1). Time points of measurement are the screening (T1), prior to the assessment in the IG and a comparable time point in the ACG (T2), after the assessment in the IG and at a comparable time point in the ACG (T3). Then approximately 6 weeks after T3 and after symptom-specific digital interventions, a further measurement will take place (T4). Another 6 weeks later a follow-up measurement will take place (T5). A last measurement time point (T6) will be conducted 6 months later with some selected participants. All time points of measurement are included in the study flow chart (Fig. 3).

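### The detectable effect printed as d = 0.15 does not match 68% power with 66 per arm; 0.15 is probably a mislabelled or misconverted effect size, and the detectable difference is about two to four times larger

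*Protocol article*

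**What the plan says.** The Sample size planning section of the protocol article has one sample size statement. It sets "a power of 68%, a sample of *N* = 132", split as "n* = 66 in the IG and *n* = 66 in the ACG", at alpha 0.05, and says that this number "is required to be able to demonstrate an effect of *d* = 0.15". Significance is judged by a "p*-value of a two-sided test below 0.05". The calculation is described as "repeated-measures MANOVA: within-between interaction; power analysis calculated with G*Power".

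The section gives no number of measurements, within-person correlation or SD for the calculation. The Evaluation concept section describes the design as one "with a three-group pretest–posttest procedure", which suggests two measurements. The same section schedules T1 to T5, and a T6 for selected participants only.

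**The concern.** The symbol d normally means a difference between two group means in SD units. A difference of 0.15 SD is very small, and 66 patients per arm are far too few to show it with 68% power in an ordinary two-group comparison. Repeated measurements can raise power, but only a very high within-person correlation would raise it that far.

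The statement matters because symptom reduction is a primary endpoint and this is the only place where the article says what size of effect the trial can show. A reader who takes it literally could treat a null result as evidence against even very small benefits. At correlations up to 0.7 the trial would miss a true 0.15 SD difference at least four times in five.

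**Working it through.** **Inputs from the article.** Two-sided alpha 0.05; 66 per arm, N = 132; effect 0.15, labelled d; group-by-time (within-between) interaction test; stated power 68%.

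**Assumptions, because the article gives no values.** Number of measurements m from 2 to 6; within-person correlation rho from 0 to 0.9, equal between all measurements; equal SDs; no group difference at baseline. Power comes from the noncentral F distribution with noncentrality lambda.

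**1. Can the 68% be reproduced?** In the usual form for the within-between interaction, lambda = f² × N × m / (1 − rho).

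- f = 0.15, m = 2, rho = 0: lambda = 0.0225 × 132 × 2 = 5.94. On F(1, 130), power is 67.7%. This matches the stated figure.
- f = d/2 = 0.075: 68% is reached at rho = 0.75, 0.70, 0.65, 0.61 and 0.56 for m = 2, 3, 4, 5 and 6.
- MANOVA index f(V) = 0.15: 40% at m = 2, falling to 21% at m = 6. With f(V) = 0.075 it is 14% or less. Neither reproduces the figure.

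**2. What group difference do those inputs mean?** With two groups and two measurements, a difference in change of D outcome SDs gives an interaction f of D/4, so D = 4f.

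- f = 0.15: D = 4 × 0.15 = 0.60 SD.
- f = 0.075, m = 2: D = 4 × 0.075 = 0.30 SD.
- f = 0.075, m > 2, same difference D at every follow-up: f = (D/2) × √(m − 1)/m, so D = 0.15 × m/√(m − 1). This gives 0.32 SD at m = 3 and 0.40 SD at m = 6.
- f = 0.075, m = 3, difference growing linearly: about 0.37 SD at the last measurement.

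In none of these is 0.15 the group difference in SD units.

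**3. Power if the true difference is 0.15 SD.**

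- Two-sample comparison, one time point: lambda = (66/2) × 0.15² = 33 × 0.0225 = 0.74, power 13.7%.
- Two-measurement difference in change: lambda = 0.0225 / [(2/66) × 2(1 − rho)].
- Five measurements (T1 to T5), 0.15 SD at every follow-up: multivariate interaction test.

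| rho | two measurements | five measurements |
|---|---|---|
| 0 | 9.3% | 8.0% |
| 0.5 | 13.7% | 11.4% |
| 0.7 | 19.7% | 16.5% |
| 0.8 | 27.2% | 23.4% |
| 0.9 | 48.1% | 45.0% |

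Three measurements give 49.0% at rho = 0.9. If the difference instead grows linearly to 0.15 SD, power with three or more measurements is lower than under the constant pattern. With two measurements, 68% is reached only at rho of about 0.94.

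**4. Difference detectable with 68% power at 66/66.** The noncentrality needed on F(1, 130) is 5.98. For a two-measurement difference in change, D = √[5.98 × (2/66) × 2(1 − rho)]:

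- rho = 0: 0.60 SD
- rho = 0.5: 0.43 SD
- rho = 0.7: 0.33 SD

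Relative to 0.15, these are factors of 4.0, 2.8 and 2.2. The f = 0.075 reading with two measurements (rho 0.75, 0.30 SD) gives a factor of 2.0.

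**The case against.** The strongest reply is that nothing was miscalculated. G*Power's repeated-measures procedures take an index from the f family, and f = 0.15 with two measurements and zero correlation returns the stated power almost exactly. A reader might infer from the low power figures that the 68% is itself false arithmetic; the article does not support that, since inputs exist that produce it.

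A second reply keeps the label. The common two-group conversion f = d/2 turns d = 0.15 into f = 0.075, and 68% then follows at unremarkable correlations of 0.56 to 0.75. This also stands as arithmetic. But that conversion is for a comparison of two means. In a group-by-time interaction with two measurements, f = 0.075 is a 0.30 SD difference in change. Either way the printed d is not the detectable group difference.

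A third reply is that a condensed article may leave the number of measurements and the correlation to the full protocol. That is accepted, and their absence is not the complaint. The complaint is that the printed value fails across the correlations tried, from 0 to 0.9.

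A reader might also infer that the trial needs about 524 patients per arm, from 2 × (1.96 + 0.468)² / 0.0225. That figure is for a single-time-point comparison, or for change scores at correlation 0.5. It is not for the named test in general, and the article does not show that 0.15 SD was the intended target.

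**Conclusion.** The point holds for the printed detectable effect. With 66 per arm and two-sided alpha 0.05, a 0.15 SD group difference has 13.7% power in a two-sample comparison. In the group-by-time test with a constant difference after baseline, it has about 8 to 20% at correlations of 0 to 0.7, about 22 to 27% at 0.8, and 45 to 49% at 0.9 with two to five measurements.

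An effect-size label or conversion error is the most likely cause, but that is an inference from which inputs return 68%. The failure of 0.15 as a group difference does not depend on it.

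The difference detectable at 68% power is about two to four times the stated 0.15. That factor covers the input sets that return 68% and correlations from 0 to about 0.75. It changes with the number of measurements and the effect pattern, and it would be smaller at higher correlations, for which the article gives no basis.

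**What to change.** In Sample size planning, replace the d = 0.15 statement with the index actually entered in G*Power (f, f(V) or d), the number of measurements and the assumed within-person correlation. Then restate the detectable between-group difference in outcome SD units under those inputs. For a two-time-point difference in change at 66/66, this would be about 0.60, 0.43 or 0.33 SD at correlations of 0, 0.5 or 0.7. These values are examples only; an analysis with more measurements needs its own figure and a stated effect pattern. Drop the claim that a d of 0.15 can be shown with 68% power.

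The cost is wording and one rerun of the calculation. No patients are added. The stated detectable effect becomes less favourable.
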